**Part 3 — Exploring stakeholder views and experiences**			
Feasibility and acceptability of trial procedures through qualitative data	Interviews will explore patients’ willingness to be randomised; patients’ views on trial recruitment and retention strategies, preferences, barriers, and facilitators to trial recruitment and retention; importance and acceptability of outcome measures	3-month and 6-month interviews with patients and interviews with intervention providers	Part 3 Objective 1
Operational issues in the delivery of cognitive screening and management pathway	Contextual factors which influence intervention and pathway delivery, including mechanisms which influence its affect and outcomes; behavioural elements of the intervention, essential resources needed, and barriers to screening and intervention delivery Reviewing notes from monthly teleconferences/videoconferences with clinicians and supervision sessions with intervention providers and the part 3 interviews	Throughout data collection (notes) 3-month and 6-month interviews with patients and interviews with intervention providers and clinicians	Part 3 Objectives 2, 3, 4, and 6
Patient, intervention provider and clinician experiences of cognitive screening and management pathway	Engagement with the pathway; mechanisms considered important in determining key outcomes: Reviewing notes from monthly teleconferences/videoconferences with clinicians and supervision sessions with intervention providers and the part 3 interviews	Throughout data collection (notes) 3-month and 6-month interviews with patients and interviews with intervention providers and clinicians	Part 3 Objectives 2, 3, 4, and 6
Intervention provider experiences of training	Interviews to explore intervention providers’ readiness to deliver NEuRoMS intervention following training; potential contamination issues; potential improvements to training: reviewing training feedback forms, supervision sessions with intervention providers, and part 3 interviews with intervention providers	Throughout data collection (notes) Interviews with intervention providers	Part 3 Objectives 5 and 6

In addition to feasibility outcomes, the following measures will also be used to capture information about the part 2 participants at baseline and 3 and 6 months after randomisation:Cognitive impairment assessed using Perceived Deficits Questionnaire [30]Quality of life assessed using Multiple Sclerosis Impact Scale [31] and EQ-5D-5L [32]Mood assessed using Patient Health Questionnaire-9 [33], Generalised Anxiety Disorder-7 scale [34], and Whooley Questions for depression screening [35]Functional ability assessed using Nottingham Extended Activities of Daily Living Scale [36]Self-efficacy assessed using Multiple Sclerosis Self-efficacy Scale [37]Service-use questionnaire, based on a measure used in other MS trials [38] and adapted for use in the NEuRoMS projectWork-related issues assessed using Multiple Sclerosis Work Difficulties Questionnaire Short Form [39]The extent to which work and medication adherence have been impacted by cognitive problems assessed using two single bespoke questionsCapability and wellbeing for health economics evaluation assessed using the ICEpop CAPability measure for Adults (ICECAP-A) [40].

We chose these measures because they (i) tap the domains of interest identified by our patient and public involvement (PPI) group (ii), were endorsed by our PPI partners, (iii) have good psychometric properties and are routinely applied in MS research, and (iv) are brief and easy to complete.

### Data collection

Part 1 involves an observational study of those who receive cognitive screening and support, using routinely collected screening data. Observations of how people use and interact with screening will include anonymised usage data (e.g. duration, mode of completion, frequency and type of support received to aid completion, and the reminders required to complete screening) and screening scores from the completed screening tasks from those who gave consent.

Monthly teleconferences/videoconferences between a member of the research team and clinicians at the three MS clinics will also be documented with detailed notes recorded by the researcher and used as a data source. These conversations will explore any problems with implementation, possible solutions, and what is working well and why.

In part 2, once the participant has been recruited and consented, they will complete the demographics form and baseline questionnaires either online, over the phone with a member of the research team, or using postal paper copies. Participants will complete the same questionnaires at 3- and 6-month post-randomisation. Independent researchers, blinded to treatment allocation, will support participants who require help completing the questionnaires over the telephone and will contact participants to complete any missing questionnaire data.

We will keep a record of any intervention contamination. Contamination will be minimised by having only specific intervention providers deliver the intervention for the trial. Intervention providers will be specifically trained to deliver the intervention, and only they will have access to the intervention tools via a password-protected website. The intervention providers will only provide care to intervention group participants and not to control group participants. We acknowledge some contamination may occur if people with MS share information with others, but as the intervention is individually tailored and delivered one to one, the potential for contamination at a participant level is small. Therefore, we will assess to what extent all participants in both control and intervention groups received the NEuRoMS intervention by reviewing clinical notes and service-use questionnaire and through monthly supervision and mentoring sessions and part 3 interviews.

In part 3, semi-structured interviews will be undertaken with part 2 participants, clinicians involved in delivering the NEuRoMS cognitive screening and management pathway, and intervention providers. Interviews will explore the cognitive screening and management pathway, components of the intervention, and research processes, to refine the pathway, intervention, and programme theory prior to the definitive trial. Control participants will also be interviewed about their feelings about not being randomised to the intervention group, what we can do to improve return of questionnaires, and what care they received (to characterise usual care and assess any contamination). We will also enquire about participants’ experience of receiving their screening results. To aid participant recall, we will collect qualitative data from patient participants at two time points: after completion of 3-month follow-ups to gather feedback on the intervention and after completion of 6-month follow-ups to gather feedback on outcomes.

Interviews will mostly be conducted over the phone/videoconferencing; however, patient participants can request to be interviewed in-person. Semi-structured interview guides will be sent to patient participants ahead of the interview to foreshadow what the interview will cover. Interviews will be audio recorded and transcribed verbatim by an approved transcription service. Interviewers will keep field notes to capture contextual information. The interviewer will have a good understanding of the screening and intervention, but will not be directly involved in delivering either.

### Adverse events

The occurrence of an adverse event (AE) or serious adverse event (SAE) because of study participation is unlikely since the study involves completing standardised tasks and questionnaires and receiving a manualised non-pharmacological intervention with trained professionals. Indeed, this has been the case in other MS trials of a similar intervention [38]. AEs and SAEs such as hospitalisation, distress, and death, in relation to participating in this study, will be recorded; however, these are likely to be rare events due to the nature of the study. ‘Notable events’ (i.e. any events that are considered out of ordinary) occurring during cognitive screening, or the intervention, will be recorded and monitored by the intervention providers or researchers. Participants will be informed of all research activities prior to participating in the study; thus, there will be no deception.

The results of the screening will be discussed with the patient by a healthcare professional, and, therefore, any concerns about the screening results will be addressed by the clinician. It is possible that talking about cognitive difficulties may sometimes create distress for people with MS. This distress will be dealt with during the intervention sessions or interviews on an individual basis. The intervention will be delivered in a clinical environment by a trained intervention provider who will receive monthly supervision. Therefore, the overall risk has been assessed as minimal.

If a participant is identified as having a high score on the Patient Health Questionnaire-9 and Generalised Anxiety Disorder-7 scale as part of the part 2 patient-reported outcomes (≥ 15 indicative of severe anxiety and depression [41]), we will recommend that they contact their GP to discuss this further. This will not affect their participation in the study, and GPs will already be aware of patients’ involvement in the part 2 study.

If a participant discloses information during the intervention sessions or during interviews indicating that they are at risk of self-harm, or discloses information about intention to harm others, the intervention provider and interviewer will follow the safeguarding policies of their employing organisation or local NHS Trust standard procedures. If the participant has responded to question 9 of the Patient Health Questionnaire-9 (“How often have you been bothered with … thoughts that you would be better off dead, or of hurting yourself”) with answer 3 (“Nearly every day”), when checked by the research team, this will be interpreted as a significant suicide risk and documented as an AE. The researcher will report the suicide risk to the principal investigator (PI) immediately. The PI/person delegated by PI will then deal with the situation as per local NHS Trust standard procedures. AEs and SAEs will be reviewed and monitored by the independent programme steering committee.

The interviews will be conducted by trained researchers who will follow a distress protocol in the event of distress during interviews [42]. Researchers will ensure they give sufficient time to participants for debriefing after the intervention sessions/interviews. Participants will be informed that they can end the study at any point. If the participant no longer wishes to continue and consent is withdrawn, the researcher will debrief the participant and provide support, as needed.

Patient participants will be advised in the participant information sheet to contact their general practitioner (GP) (and/or their occupational health/counselling services for clinician and intervention provider participants) if they feel distressed. Contact information of appropriate sources of support will be provided for patient participants who feel they need further information/support with respect to cognitive problems in MS. Participants and GPs of patient participants will also receive the contact details of the research team for enquiries about the research.

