### Randomisation and blinding

In the feasibility RCT, once the participant has been recruited, consented, and completed the baseline questionnaires, we will individually randomise them to control or intervention groups (ratio 1:1, stratified by study site), using an online dynamic adaptive algorithm [28], developed and maintained by the North Wales Organisation for Randomised Trials in Health (NWORTH) Clinical Trials Unit (CTU).

Blinding will not be possible for the participants and intervention providers due to the nature of the intervention. Research staff who are analysing the data will remain blind to allocation. Most outcome data will be self-reported and collected using online or postal questionnaires. Questionnaires collected over the phone will be collected by an independent researcher who will request participants not to reveal their group allocation or discuss their study involvement. At each assessment time point, the independent researcher will be asked to record if they were unblinded to group allocation, and if so, the reasons for this.

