### Intervention and usual care groups

All participants will have completed the online cognitive screening process (part 1) pre-randomisation. Cognitive screening is a new clinical procedure at each site involving a self-administered, brief online screening tool (completed at home prior to clinic visit or completed in clinic prior to routine neurology appointment) that can be administered with minimal support from clinical staff. The screening tool consists of computerised tasks (e.g. symbol substitution task which is a version of the Symbol Digit Modalities Test and/or word colour test which is a version of the Stroop test) that capture cognitive functions (information processing and attention) and brief questionnaires, assessing mood, fatigue, and self-reported cognitive function from the Multiple Sclerosis Quality of Life Inventory [29]. Test and questionnaire scores will be automatically calculated by the online system and transferred to the clinical team. This new clinical procedure will form part of routine care and will help identify cognitive problems and facilitate discussions between patients and clinicians, to encourage joint decisions about appropriate management for these problems.

In part 2, the intervention group will receive usual care plus the NEuRoMS cognitive management intervention. The control group will receive usual care only. The NEuRoMS intervention is a therapist-led, manualised, and multi-faceted programme, involving various components (e.g. information provision, goal setting) and a range of strategies and techniques (e.g. psychoeducation, compensatory strategies, boosting cognitive reserve). The intervention is person centred, tailored to the needs and lifestyle of each participant, and aims to help people with MS cope with and manage cognitive problems by establishing strategies that can be maintained once the intervention sessions are completed.

The intervention will be delivered by a trained therapist (i.e. intervention provider), under the supervision of a clinical psychologist or occupational therapist. In-person, videoconferencing, and telephone delivery options will be available. The duration of the intervention will be up to 4 h, spread across up to 6 sessions. We anticipate these sessions to occur over a 2-month period, based on patient availability.

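### Adverse events are filtered on relatedness before they are recorded, and after randomisation the notable-event route is open in the intervention arm only

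*Protocol article*

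**What the plan says.** All the recording rules stand in the Adverse events section of the protocol article.

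- General rule (first paragraph): "AEs and SAEs such as hospitalisation, distress, and death, in relation to participating in this study, will be recorded".
- Notable events, meaning anything out of the ordinary (same paragraph): those "occurring during cognitive screening, or the intervention, will be recorded and monitored by the intervention providers or researchers".
- Named trigger (fourth paragraph): if a participant gives the highest answer to item 9 of the PHQ-9, "this will be interpreted as a significant suicide risk and documented as an AE". No relation to the study is required.
- Disclosures of intended harm to self or others (same paragraph): the routes named are intervention sessions and interviews.

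AEs and SAEs then go to the independent programme steering committee for review and monitoring.

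Three statements elsewhere fix who can be observed and when. On screening: "All participants will have completed the online cognitive screening process (part 1) pre-randomisation". On the comparator: "The control group will receive usual care only". On provider contact: "The intervention providers will only provide care to intervention group participants and not to control group participants".

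**The concern.** Two features of these rules work against a usable harms record.

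First, a causal judgement comes before the data. A death or hospital admission that someone thinks unconnected with the study is, on the natural reading, not recorded as an AE or SAE. The steering committee can review only what has been recorded, so it cannot check the events left out.

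Second, part of the capture depends on contact that only one arm has. If events were set out by arm, more of them in the intervention arm could reflect more observation and not more harm. The section itself foresees that discussing cognitive difficulties can be upsetting, so distress is an expected harm, and it is one that sessions are well placed to bring to light.

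The wider stake is the definitive trial. This study exists to settle procedures for it, and a recording rule that differs in practice by arm could be carried forward.

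**Working it through.** The article states no event rate and no harms calculation, so there is no figure to reproduce. The check compares the recording routes and counts scheduled contacts.

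**1. When each route is open**

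| Route | Relatedness required? | Before randomisation | After: intervention | After: control |
|---|---|---|---|---|
| AE/SAE general rule | Yes | Not specified | Nominally yes | Nominally yes |
| Notable events | No | Yes (screening) | Yes (sessions) | No |
| Self-harm disclosure | No | No | Sessions and interviews | Interviews only |
| PHQ-9 item 9 | No | Yes (baseline) | Yes (3, 6 months) | Yes (3, 6 months) |

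The notable-event row follows from three statements: screening is complete before randomisation, controls receive usual care only, and providers treat only the intervention arm. No assumption is needed.

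The PHQ-9 row follows from the Outcomes section (questionnaires at baseline, 3 and 6 months) and from Randomisation and blinding (baseline questionnaires are completed before allocation).

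**2. Scheduled contacts after randomisation, per participant**

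- Control: 2 questionnaire time points = 2.
- Intervention: 2 questionnaire time points + up to 6 sessions ("The duration of the intervention will be up to 4 h, spread across up to 6 sessions") = up to 8.
- Interviews (Sample size section) add up to 2 contacts each for 10 control and 15 intervention participants.

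**3. The same by arm, taking 60 participants at 1:1 as 30 per arm**

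- Questionnaires: 30 × 2 = 60 contacts in each arm.
- Sessions: at most 30 × 6 = 180 in the intervention arm. At the approximately 4 sessions each that the Fidelity evaluation section anticipates, 30 × 4 = 120.
- Interviews: up to 10 × 2 = 20 control and 15 × 2 = 30 intervention.

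Controls are therefore in contact with the study, but not through the route by which notable events are logged.

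**4. The two AE rules side by side**

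The general rule requires a relation to participation. The item 9 rule does not, and it can be met before allocation. If both feed one set of AE records, that set holds events selected on presumed cause together with events that were not, some of them possibly pre-randomisation.

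**The case against.** The strongest reply has four parts.

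*Harms drive no stated decision.* They are not among the endpoints in Tables 3 and 4, no between-arm comparison of events is described, and the numerical progression criteria are recruitment and retention. This stands, and it limits the severity.

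*Notable events monitor delivery.* Confining them to screening and the intervention suits that purpose. This is fair, but the rows are then not comparable between arms and should be labelled so.

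*The item 9 rule is an addition to the general rule.* It can be read as a named AE and not a contradiction. That reading is reasonable. It still leaves two admission conditions that need to be reconciled.

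*This is a condensed article.* Definitions and event forms may sit in the full protocol. That would answer a complaint about missing detail, but the relatedness condition and the notable-event window are stated here.

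A reader might also infer more than the text supports:

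- That unblinded staff judge relatedness. The article says "Blinding will not be possible for the participants and intervention providers due to the nature of the intervention", but names no one as judge, and telephone questionnaires are collected by independent, blinded researchers.
- That controls go unobserved. They complete questionnaires at 3 and 6 months, and some are interviewed.
- That a harm classed as unrelated would be invisible. Effects on mood or service use could still appear in the questionnaire summaries by group, though not as AEs.
- That a spurious excess of some given size will result. The article gives neither event rates nor detection rates, so any such ratio would be chosen and not derived.

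**Conclusion.** The concern holds in a limited form, and its severity is minor.

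- **Certain from the text:** after randomisation, notable events and in-session disclosures can be captured in the intervention arm through a route that controls do not have. The item 9 rule omits the relatedness condition of the general rule and can apply before allocation.
- **Natural reading:** relatedness filters AEs and SAEs before recording. The word *only* is not in the text, but the sentence is hard to read otherwise.
- **Inference:** AEs and SAEs are captured unequally by arm. The rule nominally covers both, but an event under usual care is hard to class as related to taking part, and the providers see one arm.
- **Not affected:** the item 9 route, which is the same in both arms.

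The size of any distortion cannot be given. What can be given is the difference in opportunity: up to 8 scheduled contacts per intervention participant against 2 per control, interviews aside. In a 60-person feasibility trial of an intervention assessed as minimal risk, this calls for clearer wording and recording; it does not call the design into question.

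**What to change.** 1. Record deaths, hospitalisations and reported distress from randomisation to 6 months in both arms, regardless of presumed relation to the study. Use sources the article already plans for both arms: the service-use questionnaire, clinical notes, PHQ-9 and GAD-7. This assumes that the service-use questionnaire asks about admissions; the article does not list its items.
2. Judge relatedness afterwards, as a separate field, and state who judges it.
3. Report events found only through session contact apart from those found by the common route. Report baseline PHQ-9 item 9 responses apart from post-randomisation events.
4. Reconcile the general AE rule with the item 9 rule, so that it is clear whether relatedness is a condition for recording.

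The change concerns recording and reporting only; it leaves the handling of distress or risk as it is. It costs protocol wording, an extra field on the event form, and some more events to log and review among 60 participants, most of them likely to be unrelated to the study.

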### Sample size

Based on reduced screening throughput at each site during the pandemic, and which now persists, we estimate that 930 patients will receive the cognitive screening link as part of their newly introduced clinical care (part 1) in 6 months.

We will recruit 60 participants to the part 2 feasibility RCT. Recommended sample size for feasibility RCTs range between 24 and 50 [26]. We believe 60 participants will enable us to optimally address the aims of this study and provide us with parameter estimates to confirm our sample size calculations for the definitive trial.

In part 3, we will interview 25 patient participants from the feasibility trial (10 from control group and 15 from intervention group) at two time points: after 3-month follow-up (time point no. 1) and after 6-month follow-up (time point no. 2). Additional interviewees will be recruited at time point no. 2 if there are dropouts. We will also interview 9 clinicians (three from each site) and the 3 intervention providers (one from each site). Sample sizes for the interviews are based on extant literature, which suggest these numbers will offer ‘theoretical sufficiency’ to answer specific questions [27] and inform the ongoing development of NEuRoMS. The sample size for the intervention providers is limited because there will only be three providers.

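### PHQ-9 item 9 has a stated action only at answer 3, so answers 1 or 2 with both scale totals at 14 or less trigger no stated response

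*Protocol article*

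**What the plan says.** All the rules are in the protocol article, Adverse events section.

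- **Item-level rule.** If PHQ-9 item 9 is answered 3, the near-daily answer, "when checked by the research team, this will be interpreted as a significant suicide risk and documented as an AE". The researcher reports it to the principal investigator at once, and "The PI/person delegated by PI will then deal with the situation as per local NHS Trust standard procedures". No action is given for answers 1 or 2.
- **Total-score rule.** "If a participant is identified as having a high score on the Patient Health Questionnaire-9 and Generalised Anxiety Disorder-7 scale", with a cut-off of 15 or more, then "we will recommend that they contact their GP to discuss this further".
- **Safeguarding.** Self-harm risk disclosed in an intervention session or an interview is handled under the safeguarding policies of the employer or the local Trust. A questionnaire answer is not among the listed routes.
- **General cover.** The information sheet tells patients to contact their GP if distressed. GPs know of their patients' part 2 involvement. Screening results are discussed with the patient by a healthcare professional.

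Under Outcomes, the PHQ-9 and GAD-7 are among the measures that "will also be used to capture information about the part 2 participants at baseline and 3 and 6 months after randomisation". Under Sample size: "We will recruit 60 participants to the part 2 feasibility RCT". Under Randomisation and blinding, most outcome data come from online or postal self-report.

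**The concern.** The article is specific about item 9. It gives the item, the answer code, the adverse event classification, the reporting line and the follow-up. Someone checking questionnaires against this text would act on answer 3 and would find no instruction for a less frequent positive answer. Such an answer counts only through the PHQ-9 total, and that total prompts action only at a level the article itself labels severe.

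At stake is the response to a participant who tells the study, on a study form, of thoughts of self-harm on some days. Because most forms are completed online or by post, often nobody is speaking with the participant when the answer is given. Followed as written, the rule lets that form be checked and filed with no contact prompted by the answer.

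**Working it through.** The plan has no figure of its own to reproduce here. The check sets the stated rules side by side and asks whether the uncovered combination can occur.

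**Inputs**
- Item 9 trigger: answer 3 (Adverse events).
- Total-score trigger: 15 or more, PHQ-9 and GAD-7 (Adverse events).
- Participants: 60 (Sample size). Time points: 3 (Outcomes).
- Assumption: all nine PHQ-9 items are scored 0 to 3. The article shows only answer 3.

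**Step 1: decision table**

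| Item 9 answer | PHQ-9 and GAD-7 totals | Action triggered by the questionnaire |
|---|---|---|
| 3 | any | Adverse event entry, immediate report to the principal investigator, local procedures |
| 1 or 2 | both 15 or more | GP advice |
| 1 or 2 | one 15 or more, the other 14 or less | GP advice if the cut-off applies to each scale; none if both scales must be high |
| 1 or 2 | both 14 or less | None, on either reading |

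The last row is the point, and it does not depend on how the total-score rule is read.

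**Step 2: can the last row occur?** The other eight PHQ-9 items carry at most 8 × 3 = 24 points.
- Item 9 = 1: the total stays at 14 or less if the other eight sum to 0–13, giving totals of 1 to 14. Reaching 15 takes 15 − 1 = 14 of the 24 points, a mean of 14/8 = 1.75 per item.
- Item 9 = 2: the total stays at 14 or less if the other eight sum to 0–12, giving totals of 2 to 14. Reaching 15 takes 15 − 2 = 13 of the 24 points, a mean of 13/8 = 1.625 per item.

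The combination is possible over a wide range of totals whenever the GAD-7 is also 14 or less.

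**Step 3: how many forms fall under the rule?** 60 × 3 = 180 planned questionnaire sets. This counts forms governed by the rule, not forms in the last row.

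**Step 4: does safeguarding close the gap?** It is triggered by disclosure in a session or interview.
- Baseline forms are completed before randomisation, so no trial session or part 3 interview has yet taken place.
- Control participants have no intervention sessions. With 1:1 allocation, about 60/2 = 30 are controls, and 10 of them are planned for interview. Roughly 30 − 10 = 20 would have neither a session nor an interview.

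The questionnaire rule is the same in both arms. For some participants, though, the safeguarding route is not available at all.

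**The case against.** The strongest reply is that this is a condensed article. It says what answer 3 sets off. It does not say that answers 1 and 2 are disregarded, and its reference to checking by the research team implies a procedure that is not reproduced. Where to place a clinical threshold is also a clinical judgement, and nothing in the document contradicts answer 3 as the level for an adverse event entry and an urgent report. Both arguments have force. A reader might infer that lower answers are ignored in practice or that these participants are unprotected, and the document does not support that. What remains is that the article prints a safety threshold in full operational detail and gives no lower tier.

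The existing cover is also more than the information sheet. GPs are aware of part 2 involvement. Every part 2 participant has completed a screening that includes mood questionnaires, with scores sent to the clinical team and results discussed by a clinician. Distress related to participation is recordable as an adverse event, and such events go to the independent steering committee. This limits the concern, but none of it is prompted by an item 9 answer. The screening mood measure is not PHQ-9 item 9, and no repeat at follow-up is described.

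A reader might also take the word joining the two scales in the total-score rule to mean that GP advice needs high scores on both. That is not well supported: the bracketed cut-off names two conditions beside two scales, and the natural reading is that it applies to each. It is at most an optional wording clarification and not a separate defect.

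**Conclusion.** The point holds as a minor participant-safety improvement. As written, item 9 answers 1 or 2 with both totals at 14 or less trigger no stated response. Here that means no response prompted by the answer; it does not mean no cover at all.

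The arithmetic shows only that the situation can arise. It rests on 0–3 item scoring and says nothing about frequency. The article gives no score distribution, so no number of affected participants can be claimed, and the 180 sets should not be read as one. A fuller protocol or local checking instruction may already deal with lower answers. The feasibility endpoints, the progression criteria and the planned analyses are unaffected.

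**What to change.** In the Adverse events section, keep the adverse event entry and immediate report to the principal investigator for answer 3, and add after it: *For answers 1 or 2 we will at least recommend that the participant contacts their GP, whatever the total score.* The clinical leads may prefer a stronger step, such as review by the principal investigator. If a fuller procedure already covers these answers, a short reference to it would do instead.

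Optionally, say in the total-score rule that a score of 15 or more on either scale alone leads to GP advice.

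The cost is one sentence (two with the option) and a matching line in the questionnaire-checking instructions. The team already checks item 9, so no new data are needed. The downside is a few more GP recommendations.
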